### Justification for the EMA sample size

As the EMA is the most burdensome aspect of our study protocol, we carefully evaluated the feasibility of utilizing a subsample of the study population for this component. The primary objective of the EMA is to investigate the cross-lagged effects between sleep parameters and affect during therapy using a Random Intercept Cross-Lagged Panel Model (RI-CLPM). To determine the appropriate sample size for our analysis, we conducted a power analysis using the powRICLPM package in R, following the procedures outlined by Mulder (2023) [91]. The parameters for our analysis included 14 time points, an intraclass correlation coefficient (ICC) of 0.3, a correlation between random intercepts (RI_cor) of 0.3, a within-group correlation of 0.5, and expected effect sizes indicated by a correlation matrix with a moderate effect size of 0.4 for sleep and affect, as well as cross-lagged effects of 0.3. In our power analysis, we examined a sample size range from 100 to 231 participants, incrementing by 10, while employing 1000 Monte Carlo replications to ensure robust power estimates. The results indicated that a sample size of 120 participants would provide a power level of over 90%. As a result, we opted to include only 120 participants in the EMA component of the study. Following the data analysis, we will conduct a post hoc power analysis to evaluate the power of the RI-CLPM. If this analysis reveals insufficient power, we have the option to revert to a mixed model approach, which necessitates fewer participants to achieve similar power levels.

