#### Dynamics of sleep, affect, and energy levels throughout therapy

The primary objective of the EMA is to investigate the dynamic interplay between sleep, affect, and energy levels during BLT. We aim to uncover whether the antidepressant effects of BLT primarily result from improvements in mood, sleep, daytime energy levels, or a combination of these factors. For statistical analysis, we will first calculate daily averages for all momentary measures. If fewer than three measures are available for a given day, the daily average will be set to not applicable (*NA)*. To isolate within-person variability, all measures will subsequently be person-mean-centered. Additionally, baseline measures—such as depressive symptoms and sleep quality—will be grand-mean centered.

To analyze the data, we will specify a Random Intercept Crossed-Lagged Panel Model (RI-CLPM) that focuses on the relationships between sleep parameters, affect, and energy levels over time. This model will incorporate dynamic variables, specifically the person-mean centered scores for sleep parameters, affect, and energy levels measured at the day level, alongside trait variables represented by grand-mean centered scores from baseline assessments, including severity of depressive symptoms and sleep quality. The model structure will include random intercepts for each participant, autoregressive paths to assess the stability of each variable, and cross-lagged paths to evaluate how one variable at a previous time point influences another variable at a subsequent time point. To estimate the RI-CLPM, we will utilize the *lavaan* package in R, employing maximum likelihood estimation for model fitting.

Prior to model construction, we will conduct an exploratory analysis to identify the most relevant parameters related to sleep, affect, and energy levels for inclusion in the model. This step is crucial to ensure that we accurately measure the constructs involved and capture the dynamics effectively. The exploratory analysis will involve visualizations, such as time series plots, lag plots, and scatter plots, to assess relationships and patterns in the data. Additionally, we will investigate how the variables change over time, seeking patterns in daily fluctuations and overall trends throughout the therapy period. Correlations between different variables at various time scales will also be examined to identify initial relationships that could inform model selection.

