Based on the findings from the exploratory analysis, we will construct a model that best represents the dynamics of sleep, affect, and energy levels. We may incorporate covariates and trait-level variables, such as demographic factors, baseline depressive symptoms, and sleep quality, which could influence the relationships being studied. In our reporting, we will present the overall model fit indices (e.g., comparative fit index, Tucker–Lewis index, root mean square error of approximation) to assess the adequacy of the RI-CLPM. We will detail the autoregressive paths indicating the stability of each variable over time, as well as the cross-lagged paths, which reveal how changes in one variable at a previous time point influence changes in another variable at a subsequent time point. This systematic examination aims to enhance our understanding of the therapeutic mechanisms underlying BLT and how improvements in sleep, affect, and energy levels interact throughout the treatment process.

Following the data analysis, we will conduct a post hoc power analysis to evaluate the power of the RI-CLPM. If this analysis reveals insufficient power, we have the option to revert to a mixed model approach, which necessitates fewer participants to achieve similar power levels.

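### The EMA analysis centres every daily measure on the person's own mean and then fits a random-intercept cross-lagged model to the centred scores, which removes the variance the intercepts need and biases the lagged paths

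*Protocol article*

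**What the plan says.** Protocol article, section on the dynamics of sleep, affect and energy levels. Momentary scores are averaged by day, then "To isolate within-person variability, all measures will subsequently be person-mean-centered". Next, "we will specify a Random Intercept Crossed-Lagged Panel Model (RI-CLPM) that focuses on the relationships between sleep parameters, affect, and energy levels over time". The dynamic variables of that model are "specifically the person-mean centered scores for sleep parameters, affect, and energy levels measured at the day level". The same paragraph adds that "The model structure will include random intercepts for each participant, autoregressive paths to assess the stability of each variable". For estimation, "we will utilize the *lavaan* package in R, employing maximum likelihood estimation for model fitting".

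Section justifying the EMA sample size. The power run behind the 120 participants used 14 time points, an ICC of 0.3, a random-intercept correlation of 0.3, a within-group correlation of 0.5, a value of 0.4 for sleep and affect, and cross-lagged effects of 0.3. Power was reported as above 90%.

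Both sections also say that, once the data have been analysed, "we will conduct a post hoc power analysis to evaluate the power of the RI-CLPM". The consequence attached to that step is a possible change of model: "If this analysis reveals insufficient power, we have the option to revert to a mixed model approach".

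**The concern.** An RI-CLPM separates stable differences between people from day-to-day movement within people, and it does so through its random intercepts. If each participant's observed mean has already been subtracted, nothing is left for the intercepts to estimate. Each person's scores also sum to zero, which creates an exact linear dependence among the days. In addition, the observed mean contains the same daily shocks as the scores it is subtracted from, so lagged coefficients on the centred scores are biased in short series.

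The lagged paths are meant to show whether mood, sleep or energy moves first during treatment. If they are distorted, the mechanism question can be answered wrongly.

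The post hoc power step raises a second, smaller issue: it lets the model be changed once the results are known.

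**Working it through.** **Inputs.** From the EMA sample-size section: n = 120, T = 14 waves, ICC 0.3, intercept correlation 0.3, within-person correlation 0.5, cross-lagged paths (CL) 0.3. The 0.4 given for sleep and affect is read as the autoregressive path (AR). Assumed: two-sided alpha of 0.05 and within-person variance 1, so the intercept variance is 0.3/0.7 = 0.43. Scheduled EMA days are the baseline week, 1 to 3 treatment weeks and the post-treatment week: 7 + 7 + 7 = 21 to 7 + 21 + 7 = 35.

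**1. The stated power, on uncentred data.** Asymptotic standard errors of one cross-lagged path, with paths free at each wave, are 0.1000, 0.0953 and 0.0913 for n = 100, 110 and 120. Power is Φ(0.3/SE - 1.96):
- n = 100: Φ(3.00 - 1.96) = 0.851
- n = 110: Φ(3.15 - 1.96) = 0.883
- n = 120: Φ(3.29 - 1.96) = 0.908

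So 120 is the first value on the grid above 90%, and the plan's figure reproduces. It applies to a two-variable model on uncentred scores.

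**2. Complete data after centring.** Each variable's 14 scores sum to zero, leaving 13 dimensions. Two variables give 2 × 13 = 26 of 28. Simulated data confirm rank 26, against 28 uncentred. The observed person means are all exactly zero, so the likelihood can grow without limit if the intercept covariance may go negative. Set the lagged paths to zero and the intercept covariance to -(1 - e)R/14, where R is the pooled covariance of the centred scores. The negative log-likelihood is then:

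| e | -log L |
|---|---|
| 0.1 | 805.5 |
| 0.01 | 529.2 |
| 0.0001 | -23.4 |
| 0.000001 | -576.0 |
| 0.00000001 | -1128.6 |

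Each hundredfold cut in e lowers it by 120 × 2 × ½ × ln 100 = 552.6, with no floor. There is no maximum likelihood solution.

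**3. When the model does run (T = 14).**
- Complete data, intercept variance held at or above zero (15 replicates): intercept variance 0.000, AR about 0.28, CL about 0.26 to 0.27.
- 20% missing days (assumed rate, 6 replicates), same bound: intercept variance 0.000, AR 0.27 to 0.29, CL 0.25 to 0.26.
- Uncentred, complete data: AR 0.39 to 0.40, CL 0.28 to 0.30, intercept variance 0.41 to 0.49.

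**4. Bias by series length.** Pooled lagged paths on centred scores (true AR 0.40, CL 0.30):

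| Days | AR | AR bias | CL | CL bias |
|---|---|---|---|---|
| 14 | 0.279 | -0.121 (-30%) | 0.267 | -0.033 (-11%) |
| 21 | 0.323 | -0.077 (-19%) | 0.279 | -0.021 (-7%) |
| 28 | 0.344 | -0.056 (-14%) | 0.286 | -0.014 (-5%) |
| 35 | 0.357 | -0.043 (-11%) | 0.289 | -0.011 (-4%) |

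A closed form agrees. The sum and the difference of the two variables follow separate AR(1) processes with λ = 0.4 + 0.3 = 0.7 and 0.4 - 0.3 = 0.1. With P = T - 1 lagged pairs and h = 1 - (1 - λ^P)/(P(1 - λ)), the Nickell bias is -[(1 + λ)/(P - 1)]h / {1 - 2λh/[(1 - λ)(P - 1)]}. The AR bias is the mean of the two results and the CL bias is half their difference.
- T = 21: -0.0938 and -0.0553, so AR -0.075 and CL -0.019.
- T = 35: -0.0533 and -0.0325, so AR -0.043 and CL -0.010.

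**5. False reverse path.** With only x→y active, the truly null y→x path averages -0.052, -0.036 and -0.020 at 14, 21 and 35 days. It is rejected in about 44%, 36% and 21-22% of runs at nominal 5%. The active path is hardly changed (0.305 to 0.307). With both cross-lags null, rejection stays near nominal (7.6%, 6.6%, 4.8%). The error therefore appears when one variable really does lead.

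**The case against.** **Is the centring only a loose description of the model's own decomposition?** The text does not allow that reading. Centring is a separate step before modelling, the centred scores are named as the model's variables, and "The model structure will include random intercepts for each participant".

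**Might one infer that the analysis will simply fail?** Not from the documents. Days with fewer than three prompts are set to missing and treatment length varies, so complete balanced series are unlikely and the model may well run. The statistical methods section also calls the plan an initial framework open to documented modification, so a zero intercept variance could be noticed and corrected. This stands. The likelier harm is a model that runs with biased paths.

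**Is the 14-day bias the right headline?** No. Fourteen waves is an input to the power run, while collection lasts 21 to 35 days. Over that span cross-lagged attenuation is modest. The false reverse path is the more serious consequence.

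**Is the post hoc power step a rule to try another model when the first is not significant?** A reader might infer this, but the documents do not say it. Power recomputed at the planned effects with the achieved sample, waves and missingness would not depend on any p-value. Only power computed from the observed estimates would. For the same reason, no figure for type I error inflation can be derived from the plan: it would need an assumed correlation between the two tests and an automatic switch.

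**Would uncentred data be enough?** Not always. Three variables over 35 days make 3 × 35 = 105 indicators for 120 participants, so the wide model may be unstable for another reason. The fix allows for this.

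**Conclusion.** The centring point holds. As written, the plan removes the variance its random intercepts are meant to model and departs from the model for which 120 participants were justified. Unconstrained maximum likelihood has no solution with complete data. Otherwise the intercept variance collapses to zero, and over 21 to 35 days the bias is about -19% to -11% for autoregressive and -7% to -4% for cross-lagged paths. When one direction alone is active, a null reverse path is rejected in about 36% to 21-22% of runs, which misleads on which variable leads.

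These sizes rest on reading 0.4 as the autoregression, on two variables rather than the planned three, on stationary series and on pooled lagged paths. The missing-data runs are few and use an assumed 20% rate.

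The second point holds in a narrower form: the option to change model comes after the results and has no stated power inputs or threshold. If power is taken from the observed estimates, the choice of model depends on the result.

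Both points concern the secondary EMA analysis. The primary MADRS comparison is untouched.

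**What to change.** - Enter uncentred daily averages in the RI-CLPM and let the random intercepts carry the person means. Keep grand-mean centring for baseline covariates only.
- If the wide model with three variables and up to 35 days proves too large, use a dynamic multilevel model with latent person-mean centring, named in advance.
- Delete the post hoc power step in both sections where it appears. Specify the fallback model now and allow it only for non-convergence or inadmissible estimates.

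The cost is a change of wording in the analysis plan. No data collection changes, and the article reports that enrolment is still under way, so the correction can be made before the analysis.

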#### Identification of predictors of response and remission

Another aim of the study is to identify combinations of patient characteristics and behaviors that predict treatment response and remission. To achieve this, we will conduct AIC penalized bootstrapped stepwise logistic regression in both forward and backward directions, examining predictors of remission and treatment response in two separate models. The examined predictors will include:Demographic Factors: *Age, Sex, Educational Level*Clinical Characteristics: *Clinical Diagnosis, Severity of Depressive Symptoms, Diurnal Variation in Affect*Sleep-Related Factors: *Subjective Sleep Quality, Sleep Efficiency, Sleep Duration, Sleep Onset Latency, Midsleep Timing, Wake after Sleep Onset, Severity of Insomnia Symptoms, Energy Levels*Circadian Factors: *Circadian Phase, Intradaily Stability, Intradaily Variability, Phase Angle Difference between DLMO and Sleep Onset, chronotype.*Light-related parameters: *Light Sensitivity*Expectations: *Expectations of Treatment*

All predictors will be measured either at intake or during the baseline week. Prior to the stepwise regression analysis, we will assess multicollinearity by calculating the Pearson correlation coefficient and Variance Inflation Factor (VIF). Variables exhibiting a Pearson correlation coefficient greater than 0.8 or a VIF score exceeding 10 will be removed to mitigate multicollinearity and examined separately. A final competitive regression model will be run with all significant predictors.

To ensure the robustness of our models, we will run 1000 bootstrap samples and retain predictors that are significant in at least 60% of the bootstrapped samples. We will also calculate partial R-squared values for all predictors in the regression models to quantify the proportion of variance in the dependent variable explained by each specific independent variable while controlling for the influence of others. Finally, we will conduct variance partitioning to investigate the unique and shared variance explained by the predictors. By comparing the explained variance from regression models of individual predictors against those with combinations of predictors, we will compute both unique and shared variance. The vegan package in R will be used for variance partitioning, and results will be visualized using Euler plots from the Euler package.

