### Objectives {7}

The primary objective of this study is to comprehensively assess and compare the effectiveness of three distinct BLT approaches for the treatment of depressive symptoms: (1) standard home-based BLT (*Light@Home)*, (2) BLT at the *LightCafé (LightCafé)*, and (3) BLT at the *LightCafé* with personalized timing of light and darkness using BBG (*LightCafé* +).

Secondary objectives are:i.The identification of predictors of treatment response, encompassing baseline clinical characteristics, sleep metrics, circadian parameters, and light-related behaviors.ii.Elucidation of underlying mechanisms of BLT’s efficacy by investigating the contribution of circadian rhythm changes, enhancing our understanding of the complex interactions between mood, energy levels, and sleep within the context of BLT and exploration of the neural effects of BLT by studying both functional and structural brain changes before and after treatment.

Importantly, we are not testing BLT’s efficacy for specific diagnostic categories; rather, we ask whether embedding BLT within a rich psychosocial setting and personalizing its timing can amplify and prolong its antidepressant effect, all while unraveling who benefits most and through which pathways. By moving from “Does BLT work?” to “How can we make it work better, for whom, and why?”, this multicenter RCT will lay the groundwork for personalized and embedded BLT protocols and real-world clinical guidelines.

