### Eligibility criteria {10}

#### General eligibility criteria

Eligibility will be assessed during the intake by study team members trained in administering the MINI International Neuropsychiatric Interview 5.0.0 (M.I.N.I.; [69]). The inclusion criteria are as follows:Age between 18 and 65.Diagnosis of unipolar or bipolar depression (seasonal or non-seasonal) confirmed by the M.I.N.I. [69].Currently experiencing a depressive episode, as indicated by a Quick Inventory of Depressive Symptomatology Self-Report (QIDS-SR; [70]) score of 6 or higher.Proficiency in either Dutch or English is required for questionnaire completion.

Participants are excluded from participation if they:Are currently experiencing a (hypo)manic or mixed episode, as determined by the M.I.N.I. assessment [69].Are presently in a psychotic episode, as determined by the M.I.N.I. assessment [69].Exhibit significant active suicidality, indicated by a score of 10 or higher on the M.I.N.I. module [69].Initiated antidepressant therapy (including medication, psychotherapy, BLT, or other specific depression treatments) within the last 2 months prior to study enrolment.Have a bipolar disorder but are currently not under mood-stabilizing treatment for at least 1 month at the recommended dosage.Have used melatonin or agomelatine in the past month.Are currently using antibiotics.Are currently taking medications that increase light sensitivity.Have travelled across more than one time zone in the past month or during the treatment period.Have travelled to sunny holiday destinations or engaged in outdoor winter sports in the past month.Have pre-existing eye and skin disorders such as retinitis pigmentosa, porphyria, chronic actinic dermatitis, and sun-induced urticaria.Have systemic disorders with potential retinal involvement, such as rheumatoid arthritis and systemic lupus erythematosus.Have color blindness (based on self-report).Worked night shifts within the last three months.Suffer from (retinal) blindness, severe cataracts, or glaucoma.Experience light-induced migraine or epilepsy.Are currently pregnant or have a child Younger than 18 months old.

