### Outcomes {12}

#### Primary study outcome—clinical improvement in depressive symptoms

The primary outcome of this study is the clinical improvement in depressive symptoms assessed with the Montgomery Åsberg Depression Rating Scale (MADRS; [78]) from baseline to post-treatment. Independent raters, unaware of participants’ treatment conditions and assessment points, will conduct MADRS evaluations. Other key metrics based on the MADRS include remission (participants with post-treatment scores of 10 or lower [79]) and response rates (participants with 50% reduction in depressive symptoms from baseline to post-treatment assessment).

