### Primary Study Outcome – Clinical Improvement between Treatment Conditions

To compare the three different BLT administration strategies in terms of clinical improvement (measured as the difference in MADRS scores between baseline and post-treatment assessments), we will employ a multilevel mixed-effects modelling approach. MADRS scores will serve as the dependent variable, with a fixed effects for timepoint (*pre- and post-treatment*), and the interaction between timepoint and treatment arm (*Light@Home, LightCafé*, and* LightCafé* +). Random intercepts for participants and study centers will be included to account for individual differences and center-level variability, but only if they improve model fit, as determined by evaluation of the Akaike Information Criterion (AIC) and Bayesian Information Criterion (BIC). Random slopes for time within participants will also be considered and included based on the same criteria. Socio-demographic (age, sex) will be evaluated for potential confounding effects, similar to the credibility and expectancy of the treatment arms as assessed with the CEQ. The primary analysis will focus on the interaction between timepoint and treatment arm to determine whether clinical improvement differs across the three BLT strategies. Furthermore, multilevel logistic regression will be used to test differences in response (yes/no) and remission (yes/no) between treatment arms using the same structure and procedure as above.

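### The search for response predictors uses only yes/no response and remission, although the full MADRS is collected; for modest predictors this costs roughly 12 to 30 points of power

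*Protocol article*

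**What the plan says.** The objectives section lists as its first secondary objective "The identification of predictors of treatment response, encompassing baseline clinical characteristics, sleep metrics, circadian parameters, and light-related behaviors". The section on identifying predictors meets it with "AIC penalized bootstrapped stepwise logistic regression in both forward and backward directions, examining predictors of remission and treatment response in two separate models". It names 21 baseline candidates, draws 1000 bootstrap samples, and will "retain predictors that are significant in at least 60% of the bootstrapped samples". It then promises partial R-squared, described as the "proportion of variance in the dependent variable explained by each specific independent variable while controlling for the influence of others", followed by partitioning into unique and shared variance.

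That section names no scale. The outcomes section, under metrics based on the MADRS, gives "remission (participants with post-treatment scores of 10 or lower" and "response rates (participants with 50% reduction in depressive symptoms from baseline to post-treatment assessment". In the primary analysis the score is used whole: "MADRS scores will serve as the dependent variable". Entry depends on a "Quick Inventory of Depressive Symptomatology Self-Report (QIDS-SR; [70]) score of 6 or higher" and a M.I.N.I.-confirmed diagnosis, with no minimum MADRS.

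Three other analyses come near but do not replace the search: moderation of the arm effect by baseline severity or sleep quality (circadian section), age, gender and diagnosis in the Cox model (time-to-remission section), and adherence covariates in regressions on symptom change (additional analyses).

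**The concern.** Cutting a 0 to 60 score at one point treats everyone on the same side of the cut as equal. A true predictor that would stand out against the score may fail against the cut, and the retention rule then drops it. The question of who benefits is one of the trial's main aims, many candidates are screened, and some exist only in subsamples (120 with EMA, 72 with saliva), so information is scarce to begin with.

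Two further features fit the binary outcomes poorly. Proportion of variance explained has its ordinary meaning in a linear model. Pseudo-R-squared versions exist for logistic models, but none is named. And because there is no MADRS entry floor, a participant could start at 10 or below and meet the remission definition without improving. Baseline severity could then look like a predictor of benefit partly by arithmetic.

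**Working it through.** **Inputs from the protocol.** Analysable N = 210; 210 × 1.10 = 231 enrolled. Initial depression score mean 23.4, SD 13.2; middle planned effect 0.33 (sample size section). Alpha 0.05 (statistical methods). **Assumptions.** Two-sided test; pre-post correlation 0.5; partial correlation r between predictor and post-treatment score; event rate p from 20 to 61%. The protocol gives no expected rates. The 61% is the higher remission rate of the seasonal-depression trial cited in its background.

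**The plan's own figure.** No power is stated for the predictor search. The overall 210 reproduces: with f = 0.25, power 0.90, k = 3 arms, m = 2 time points and λ = f²(N − k)(m − 1), the noncentral F gives N = 209.

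**Step 1, information kept by the cut.** Relative efficiency E = φ(z_p)² / [p(1 − p)].
- p = 0.20: 0.2800²/0.16 = 0.49
- p = 0.25: 0.3178²/0.1875 = 0.54
- p = 0.30: 0.58
- p = 0.50: 0.3989²/0.25 = 0.64
- p = 0.61: 0.62

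The loss is therefore 1 − 0.64 = 36% to 1 − 0.49 = 51%.

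**Step 2, power by formula.** For the score, ncp = √n · r/√(1 − r²). For the cut, multiply by √E. Power ≈ Φ(ncp − 1.96).

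Example, r = 0.20: ncp = 14.49 × 0.2041 = 2.958, so power is Φ(0.998) = 84%. At p = 0.25: 2.958 × √0.539 = 2.171, so power is Φ(0.211) = 58%, a loss of 26 points.

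| r (N = 210) | Score | Cut, p = 20 to 61% | Loss, points |
|---|---|---|---|
| 0.10 | 31% | 17–21% | 9–13 |
| 0.15 | 59% | 34–42% | 18–26 |
| 0.20 | 84% | 54–66% | 19–30 |
| 0.25 | 96% | 75–85% | 12–22 |
| 0.30 | 99.5% | 89–95% | 4–10 |

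**Step 3, simulation.** 1500 runs per cell, scores clipped to 0–60, baseline in every model. Linear regression of post-treatment MADRS is compared with logistic regression of response and of remission. Power is shown as score / response / remission.

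| r | Mean change 0.33 SD (4.4 points; rates 26% and 24%) | Mean change 0.8 SD (10.6 points; rates 46% and 41%) |
|---|---|---|
| 0.15 | 60 / 37 / 32% | 55 / 39 / 35% |
| 0.20 | 83 / 56 / 50% | 79 / 64 / 60% |
| 0.25 | 95 / 76 / 70% | 94 / 83 / 76% |

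Losses run from 12 points (response, r = 0.25, larger change) to 33 (remission, r = 0.20, smaller change). That largest cell has a standard error of about 2 points, and a separate run at a mean change of 4.3 gave 82 against 52%, a loss of 30.

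**Step 4, the 60% bootstrap rule.** This was simulated roughly, for one predictor plus baseline, with 150 trials of 100 bootstraps (standard error of each figure up to √(0.25/150) ≈ 4 points). Retention for score / response / remission at mean change 4.3 was 47/30/28% for r = 0.15, 73/50/39% for r = 0.20 and 94/64/60% for r = 0.25. At mean change 10 it was 45/29/25%, 69/57/47% and 93/79/66%. The loss is 12 to 34 points, much as for the single test. AIC stepwise selection among all candidates was not simulated.

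**Step 5, share already at MADRS 10 or lower.** Φ((10 − 23.4)/13.2) = Φ(−1.015) = 15.5%; 16.4% with continuity correction; 12.2% if the normal is truncated to 0–60. With an assumed SD of 8: Φ(−1.675) = 4.7%.

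**The case against.** The strongest reply is that response and remission are the stated target. The background wants patients stratified by likelihood of response, and a model of mean MADRS answers a related but different question. That stands, and is why both logistic models should stay. It does not explain why the search itself must run on the less informative outcome.

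The size is conditional, and that also stands. A reader might infer a fixed loss of 20 or 30 points for every predictor. The documents do not support this: they give no event rates and no predictor strengths, and at r = 0.10 or 0.30 the formula gives 9–13 or 4–10 points. The simulated data come from a linear normal model, which favours linear regression, and the full stepwise procedure was not tested.

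The 12–16% already at 10 or lower comes from a planning SD borrowed from another study. A normal with that SD puts about 4% of scores below zero, and at SD 8 the share is about 5%. It should not be read as a fact about this trial's participants. Baseline severity is already a candidate, so excluding them is not clearly needed.

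The scale is inferred: the mood-outcomes section also has self-rated QIDS-SR response and remission. The argument is the same for either scale. Which R-squared variant to use is a smaller matter that an analysis plan could settle.

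**Conclusion.** The point holds in a conditional form. The only planned predictor search uses two binary outcomes, defined in the outcomes section as cuts of the MADRS, while the full score is collected and modelled elsewhere. For one modest predictor (partial r 0.15 to 0.25) at N = 210, with the planning mean and SD, pre-post correlation 0.5 and event rates of about 20 to 60%, the cost is about 12 to 30 points of power. The direction was the same at every setting tested; the size was not.

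Two stronger readings are not supported: that response and remission are the wrong outcomes, and that the search will miss its true predictors. It may miss modest ones. The primary analysis is unaffected. At n = 72 and r = 0.25, even the score gives only 59% by the same formula (34–42% after the cut), so the change helps the melatonin-based predictors without making them well powered. It is worth making because it is cheap and recruitment was still open when the protocol was published.

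**What to change.** In the section on identifying predictors:

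1. Add a pre-specified linear regression of post-treatment MADRS on baseline MADRS (forced in) plus the candidate predictors. Use it for the search, with the same bootstrap stability rule.
2. Compute partial R-squared and the variance partitioning from this model.
3. Keep the logistic models of response and remission to express the retained predictors in clinical terms, and name the MADRS as their scale if that is what is meant.
4. Force baseline MADRS into the remission model, since entry sets no MADRS floor. Report how many participants scored 10 or lower at baseline.

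The cost is some wording and one more model, with no new data or visits. Its coefficients are in MADRS points, so the logistic models are still needed for the clinical message. The statistical methods section allows minor, documented modifications, and the change should be fixed before outcome data are examined.
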